### Aim, study design, and setting

CYPRO is a parallel-group, single-center, and single-blind randomized controlled superiority trial that is performed at the Valens rehabilitation clinic, Switzerland.

The aims of CYPRO are described as the following:

1. Primary aim: To investigate the effects of HIIT compared to MCT on cardiorespiratory fitness, as indicated by peak oxygen consumption (V̇O_2peak_).

2. Secondary aims: To investigate the effects of HIIT compared to MCT on peak power output (PPO), walking capacity, cognitive performance, HRQoL, fatigue, anxiety and depressive symptoms, and blood-derived biomarkers related to MS pathophysiology. Additionally, CYPRO aims to investigate the acute effects of a single HIIT session compared to a single MCT session on changes in blood-derived biomarkers.

HIIT represents the experimental condition that is hypothesized to be superior to the standard treatment MCT as an active comparator. The study design and flow of participants are illustrated in Fig. 1.

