### Outcomes

V̇O_2peak_, PPO, walking capacity, cognitive performance, HRQoL, fatigue, and anxiety and depressive symptoms are assessed by allocation-blinded outcome assessors at study entry (baseline, T_0_) and discharge after three weeks (T_4_), at least 48 hours after the last HIIT or MCT session. Venous blood samples are taken before (T_1_), immediately after (T_2_), and two hours after (T_3_) the first HIIT or MCT session, and at T_4_.

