#### Blood-derived biomarkers

Blood sampling is performed in a fasted state. Samples are obtained from the antecubital vein in supine position. To evaluate the chronic effects of HIIT and MCT on blood-derived biomarkers, resting blood samples are taken between 8:00 and 9:00 AM after ten minutes of supine rest (T_1_, T_4_). To evaluate acute effects on blood-derived biomarkers, blood samples are taken immediately after (T_2_) and two hours after (T_3_) the first HIIT or MCT session. Per sampling time point, two whole blood collection tubes (BD Vacutainer^®^, BD CPT™, 4ml), prefilled with lymphocyte separation medium, and one serum tube (tube vacutainer SSTII serum yel, 6ml) are taken.

Blood samples are analysed regarding the acute and chronic effects of HIIT and MCT on KP modulation, and surrogate markers of neurodegeneration (i.e., sNfL, glial fibrillary acidic protein (GFAP)).

Whole blood samples are centrifuged at 3500 g for 20 minutes, separating peripheral blood mononuclear cells (PBMCs) and plasma. PBMCs are resuspended in plasma, purged into centrifugation tubes, diluted with an equal amount of phosphate-buffered saline, and centrifuged at 2400 g for 10 minutes. The supernatant is discarded. PBMCs are resuspended in cell culture freezing medium, and aliquoted. Aliquots are frozen at -80 °C until analysis. mRNA of PBMCs is isolated using a commercial column-based isolation kit. cDNA synthesis is performed. Based on mRNA and cDNA, gene expression of KP-relevant genes is determined. As such, expression levels of indoleamine 2,3-dioxygenase-1, kynurenine aminotransferase 1–4, kynurenine-3-monooxygenase, aryl hydrocarbon receptor, CYP1A1, interleukin-4-induced-1, and SLC7A5 are determined using real-time quantitative polymerase chain reaction (qPCR), run on a qTower³ G touch (Analytik Jena GmbH, Jena, Germany). Blood serum is centrifuged at 2500 g for 20 minutes, is aliquoted, and frozen at -80 °C until analysis. Targeted metabolomics (liquid chromatography tandem mass spectrometry (LC-MS/MS)) is performed at BEVITAL AS, Bergen, Norway, to determine serum concentrations of tryptophan, KP downstream metabolites (e.g., kynurenine, kynurenic acid, quinolinic acid), and B vitamers. Systemic concentrations of sNfL and GFAP are assessed using a single molecule array (SiMoA HD-1 device, Quanterix, USA) at the University Medical Center of the Johannes Gutenberg University, Mainz, Germany, according to the manufacturer’s instructions.

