### Statistical analysis

Statistical analyses are performed according to the intention-to-treat principle. Descriptive statistics will be reported as arithmetic mean (*M*) and standard deviation (*SD*) for continuous data, and as absolute number and percentage (*%*) for categorical data for the total sample, and separated by group. Outcome data will be checked for normality (Shapiro-Wilk test) in advance. If necessary, analyses will be adjusted accordingly. If missing values are < 5%, ANCOVA will be performed to detect time*group interaction effects and main effects of time. In that case, effect sizes will be calculated as partial eta squared (*pη*^*2*^). Otherwise, a baseline-adjusted Mixed Model for Repeated Measures (MMRM) approach, with group, time and the group × time interaction as fixed effects (type III sums of squares, CS covariance structure over time) is used to assess between-group differences over time. Bonferroni-corrected pairwise comparisons of estimated marginal means of the group × time interaction are computed. Effect sizes will be reported as Cohen’s *d* with 95% confidence interval (*CI*). For all analyses, the level of significance is set at *p* = .05. Within-group differences and between-group differences are depicted as point estimates and measures of variability for all outcomes. Bivariate correlation analyses will be conducted to determine potential associations between changes in V̇O_peak_, PPO, walking capacity, cognitive performance, HRQoL, fatigue, anxiety and depressive symptoms, and blood-based biomarkers using Pearson’s *r*. All statistical analyses will be conducted with IBM SPSS Statistics for Windows (Version 29.0., IBM Corp., Armonk, New York, USA). Besides the final analysis, one interim analysis will be performed upon collection of 50% of participant data (HIIT: *n* = 15, MCT: *n* = 16).

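### Compound symmetry is fixed, with no alternative, for biomarker samples spaced from minutes to three weeks apart; if all four enter one mixed model, the standard errors are valid only when all variances and correlations are equal

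*Protocol article*

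**What the plan says.** The Statistical analysis section has two branches. The first reads "If missing values are < 5%, ANCOVA will be performed to detect time*group interaction effects and main effects of time". Otherwise the plan uses a "baseline-adjusted Mixed Model for Repeated Measures (MMRM) approach, with group, time and the group × time interaction as fixed effects", and the covariance is set in the same sentence: "type III sums of squares, CS covariance structure over time". No other structure, convergence fallback or robust SE is named, and outcomes are not distinguished. Inference then rests on model-based contrasts: "Bonferroni-corrected pairwise comparisons of estimated marginal means of the group × time interaction are computed".

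The Outcomes section sets the sampling times: "Venous blood samples are taken before (T_1_), immediately after (T_2_), and two hours after (T_3_) the first HIIT or MCT session, and at T_4". All other outcomes are measured only at T0 and T4.

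The samples serve two questions. In the aims, "CYPRO aims to investigate the acute effects of a single HIIT session compared to a single MCT session". For the longer-term question, the Blood-derived biomarkers section says: "To evaluate the chronic effects of HIIT and MCT on blood-derived biomarkers, resting blood samples are taken between 8:00 and 9:00 AM" (T1 and T4).

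**The concern.** Compound symmetry (CS) imposes one variance at every time and one correlation between every pair of times. T1 and T2 are separated by a session of 21 minutes (HIIT) or 26 minutes (MCT), T3 follows two hours after the session, and T4 comes three weeks later. There is no reason to expect one correlation to fit all these gaps, or the spread just after exercise to equal the spread at rest. A CS model gives every time the same averaged error variance, so a contrast whose true error is above the average gets too small an SE, and one below it too large.

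At stake is the error rate of the biomarker comparisons: false positives for some contrasts and lost power for others. These are secondary outcomes, but the Discussion relies on markers such as sNfL and GFAP when it describes the trial's contribution to exploring disease-modifying effects.

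**Working it through.** **Figures in the plan.** The article states no biomarker SE, correlation or SD by time, so there is no figure to reproduce. Its one correlation, 0.6, belongs to the V̇O2peak sample size calculation.

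**Inputs from the article.** Total 61, drop-out 15%, allocation 1:1. 61 × 0.85 ≈ 52, or 26 per arm. All biomarker correlations and SDs below are assumptions.

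**Baseline-adjusted form (T1 as covariate; T2, T3, T4 as outcomes).** Set the SD at T1 to 1. Let s_t be the SD at time t and c_t the covariance of time t with T1. With one common slope, b is the mean of c_2, c_3 and c_4. The residual variance at t is

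v_t = s_t² + b² − 2·b·c_t

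and CS replaces each v_t by their mean, so

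model SE / true SE at t = √(mean v / v_t).

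The type I error of an unadjusted two-sided 5% test is about 2·[1 − Φ(1.96 × ratio)].

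*Worked example.* Equal SDs, correlations with T1 of 0.95 (T2), 0.90 (T3) and 0.70 (T4):
- b = (0.95 + 0.90 + 0.70)/3 = 0.85
- v = 0.1075, 0.1925, 0.5325; mean 0.2775
- T2: √(0.2775/0.1075) = 1.61
- T4: √(0.2775/0.5325) = 0.72; 1.96 × 0.72 = 1.41, so type I error is about 16%

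| Assumed correlations with T1 (T2, T3, T4) | SE ratio T2 | T3 | T4 | Type I error T2 | T4 |
|---|---|---|---|---|---|
| 0.60, 0.60, 0.60 | 1.00 | 1.00 | 1.00 | 5% | 5% |
| 0.85, 0.80, 0.70 | 1.17 | 1.04 | 0.86 | 2.2% | 9.0% |
| 0.90, 0.90, 0.80 | 1.14 | 1.14 | 0.83 | 2.5% | 10.5% |
| 0.90, 0.90, 0.60 | 1.34 | 1.34 | 0.73 | 0.9% | 15.4% |
| 0.95, 0.90, 0.70 | 1.61 | 1.20 | 0.72 | 0.2% | 15.7% |
| 0.90, 0.90, 0.80, with SD ×1.5 at T2 and ×1.2 at T3 | 0.90 | 1.22 | 0.96 | 7.9% | 5.9% |
| 0.60, 0.70, 0.85 (resting samples most alike) | 0.86 | 0.98 | 1.28 | 9.1% | 1.2% |

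Simulation with 26 per arm, complete data and no true effect agrees: for the last row it gives ratios of about 0.87, 0.98 and 1.27.

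**T1 treated as an outcome (change-from-T1 contrasts, equal SDs).** The ratio is √[(1 − mean r)/(1 − r_1t)], with mean r taken over all six pairs.
- T1-T2 and T2-T3 at 0.95, T1-T3 at 0.90, all pairs with T4 at 0.70: mean r = (0.95 + 0.95 + 0.90 + 3 × 0.70)/6 = 0.8167. T2: √(0.1833/0.05) = 1.91. T4: √(0.1833/0.30) = 0.78, type I error about 12.5%.
- 0.85, 0.85, 0.80 and 0.70: mean r = 0.7667. T2: √(0.2333/0.15) = 1.25. T4: √(0.2333/0.30) = 0.88, type I error about 8.4%.

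**Ranges when same-day correlations exceed those with T4 and SDs are equal.** Over both forms, T4 ratios run from 0.72 to 0.88, so the SE is 12-28% too small. T2 ratios run from 1.14 to 1.61 in the baseline-adjusted form and reach 1.91 with T1 as an outcome.

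**Outcomes measured only at T0 and T4.** With baseline as covariate one post-baseline time remains, so there is nothing to average and CS has no effect.

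**The case against.** A reader might infer that CS will make three-week effects appear too often and hide acute ones. The article does not support that as a prediction. It gives no biomarker correlations or SDs, and the Blood-derived biomarkers section offers a reason to doubt the ordering: T1 and T4 are both fasted, supine resting samples taken at the same hour, whereas T2 directly follows exercise. The last two rows of the table show the error moving to T2 or reversing. This objection stands against any signed claim. It does not rescue CS, because those rows still contain wrong SEs.

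Three further limits stand.
- The article never says that acute and chronic effects share one model. If T4 is analysed alone with T1 as covariate, CS does no harm to the three-week contrast.
- CS applies only in the branch with 5% or more missing. Planned drop-out, with no assessments afterwards, makes that likely at T4: 9 of 61 is 14.8%. The article does not say how the percentage is counted. If every drop-out came after T3 and all four samples were counted together, it would be 9/244 = 3.7%.
- The largest acute figure, 91% too large, arises only if T1 is an outcome. The stated model is baseline-adjusted, where the upper end is about 61%.

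**Conclusion.** The point holds conditionally. The article commits to CS without an alternative, and the biomarker times are poorly suited to it. If all four samples enter one such model, the SEs of the acute and three-week contrasts are right only when all variances and correlations are equal.

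For correlations that fall across the three-week gap with equal SDs, the distortion is material: type I error of about 8-16% at T4 instead of 5%, and an acute test well below its nominal level. Under other patterns the distortion shifts to other contrasts, reverses or disappears. Since the direction cannot be known beforehand, the structure should not be fixed in this way.

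A reader might extend this to the primary result. That does not follow: V̇O2peak and the other T0/T4 outcomes are not affected.

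**What to change.** For the biomarkers, replace CS with an unstructured covariance over T2, T3 and T4. Enter T1 and T1 × time as covariates and use Kenward-Roger degrees of freedom. With complete data this reproduces the separate ANCOVA at each time, so each contrast keeps its own error variance and the nominal 5% level whatever the true correlations.

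Prespecify the fallback: if the model does not converge, fit separate baseline-adjusted models for the acute (T2, T3) and chronic (T4) questions. If separate models are already intended, say so.

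The cost is one changed phrase and 6 covariance parameters (3 variances, 3 covariances) instead of 2, affordable with about 52 to 61 participants. Data collection and the primary analysis do not change.

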### Sample size calculation

Sample size calculation for the estimated effect of HIIT or MCT on the primary outcome V̇O_2peak_ was performed using G*Power software (Version 3.1.9.7, Heinrich Heine Universität, Düsseldorf, Germany) [20]. Estimating a drop-out of 15%, a total of 61 participants (HIIT: *n*= 30, MCT: *n*= 31) was found to be sufficient to identify a small to moderate effect (*ES* ≥ 0.15) in ANOVA analysis on 2 group (HIIT vs. MCT) * 2 time (T_0_ vs. T_4_) interaction. Power was set at 80% and alpha at 0.05. Correlation among repeated measures was set at 0.6.

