#### Cardiorespiratory fitness

V̇O_2peak_ is assessed by CPET on a bicycle ergometer (ergometrics er800s, ergoline GmbH, Bitz, Germany). CPET is performed in a fasted state between 8:00 and 9:00 AM and follows a ramp-type protocol. The ramp-type protocol consists of (a) a resting state measurement without pedaling while participants are sitting on the bicycle ergometer (3 minutes); (b) subsequent pedaling at 20 watts (3 minutes); (c) the testing phase with a progressive increment of 5 to 10 watts per minute until subjective exhaustion (8-12 minutes); (d) followed by a cool-down of unloaded pedaling (3 minutes). HR is continuously monitored. Blood pressure and RPE (Borg CR-10 scale) are assessed every two minutes and within the last ten seconds of the test.

V̇O_2_ is monitored by direct and continuous measurements (breath by breath) by ergospirometry (Vyaire Medical, Vyntus CPX, Illinois, USA). V̇O_2peak_ is defined as the highest 15-second averaged V̇O value when the following criteria are attained: respiratory equivalent ratio > 1.10; HR_peak_ within 10 min^−1^ of the age-predicted maximum and Borg-CR-10 rating > 8.5 [31]. The absolute V̇O_2peak_ value (mL · min^−1^) is divided by bodyweight (kg) to obtain the relative V̇O_2peak_ value (mL · min^− 1^ · kg^− 1^) as the primary outcome.

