#### Peak power output (PPO)

PPO is assessed as the peak wattage achieved during CPET and represents the maximum mechanical power produced by lower extremity musculature. PPO is considered a measure of the physical functional reserve. In pwMS, lower PPO is correlated with higher energetic costs of walking [32].

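### The correlations between outcome changes carry no term for arm; if the arms are pooled and differ on both outcomes, r partly restates the arm comparison, modestly at the planning-scale effect

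*Protocol article*

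**What the plan says.** The method is fixed in the protocol article, Statistical analysis. "Bivariate correlation analyses will be conducted to determine potential associations between changes in" a list of outcomes that begins with peak oxygen consumption and ends with "anxiety and depressive symptoms, and blood-based biomarkers using Pearson’s *r". No partial correlation, arm covariate or within-arm analysis is named.

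Two other sentences in that section might seem to bear on the point, but do not:

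- The split "for the total sample, and separated by group" is given for descriptive statistics, not for the correlations.
- The statement that analyses will be adjusted where necessary follows the Shapiro-Wilk check and concerns non-normality, not arm.

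The significance threshold is common to everything: "For all analyses, the level of significance is set at *p* = .05".

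HIIT is hypothesised to be superior to MCT (Aim, study design, and setting). The Discussion reports that in earlier studies, in the same setting and with similar protocols, HIIT beat MCT on peak oxygen consumption and on cognitive performance, and that HIIT favourably changed biomarkers. It expects these findings to be reproduced if people with PPMS respond as mixed samples did.

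**The concern.** A correlation between two changes invites the reading that participants who gained more on one outcome also gained more on the other. In a two-arm trial, a pooled correlation mixes two things: the association among participants given the same training, and the separation between the arm means. If HIIT moves both outcomes relative to MCT, the second part alone produces a non-zero r.

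That part is the arm comparison seen again. It says nothing about whether an individual's fitness gain goes with that individual's other gain. It also grows with the arm differences, so it matters most if the trial succeeds on several outcomes. At stake is the interpretation of an exploratory analysis, not the trial's main answer.

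**Working it through.** **No figure to reproduce.** The article gives no expected size, power or sample size for the correlations. The planning effect for peak oxygen consumption is used below only to set a scale.

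**Inputs**

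- Allocation 1:1 (Recruitment and randomization procedure), so the share per arm is p = 0.5 and p(1 − p) = 1/4.
- 61 participants with 15% drop-out (Sample size calculation): 61 × 0.85 = 51.85, about 52 completers.
- Planning effect: "sufficient to identify a small to moderate effect (*ES* ≥ 0.15) in ANOVA analysis on 2 group" by 2 times, with correlation among repeated measures 0.6.
- "Power was set at 80% and alpha at 0.05" for planning; the .05 level applies to all analyses. Two-sided tests are assumed.
- Assumptions: the arms are pooled, the effect size is Cohen's f, and changes are normal with equal variance in both arms.

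**Step 1: the planning effect as an arm difference in change.** For the group-by-time interaction with m = 2 times, the noncentrality is f²·N·m/(1 − ρ). A comparison of mean change between equal arms has noncentrality N·d²/4, where d is the arm difference in SDs of change. Equating the two:

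d² = 4·f²·m/(1 − ρ) = 4 × 0.0225 × 2/0.4 = 0.45, so d = 0.67.

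Caveat: with f = 0.15, correlation 0.6, two-sided alpha 0.05 and 80% power, this model needs 72 completers, not about 52. Reading the effect size as f therefore does not reproduce the planned 61. That is a separate matter; here 0.67 is only one point on the range below.

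**Step 2: the induced correlation.** With zero correlation within each arm and arm differences d1 and d2,

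r = (d1·d2/4) / √[(1 + d1²/4)(1 + d2²/4)].

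- d1 = d2 = 0.67: 0.1125/1.1125 = 0.10.
- d1 = d2 = 1.0: 0.25/1.25 = 0.20.
- d1 = d2 = 0.3: 0.0225/1.0225 = 0.02.
- One difference zero: the numerator is 0, so r = 0.

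**Step 3: how often p < .05.** Simulation with 20,000 runs per case and no association within either arm:

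| Arm differences (SD of change) | Pooled r | Pooled, N = 52 | Pooled, N = 61 | Partial r given arm |
|---|---|---|---|---|
| 0.67 and 0 | 0.00 | 5.0% | 4.9% | about 5% |
| 0.3 and 0.3 | 0.02 | 5.2% | 5.3% | about 5% |
| 0.67 and 0.3 | 0.05 | 6.0% | 6.6% | about 5% |
| 0.5 and 0.5 | 0.06 | 6.7% | 7.3% | about 5% |
| 0.67 and 0.67 | 0.10 | 10.9% | 12.4% | 5.0% |
| 0.8 and 0.8 | 0.14 | 16.0% | 19.0% | about 5% |
| 1.0 and 1.0 | 0.20 | 30.3% | 34.9% | about 5% |

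These percentages are false positives for the question of whether the changes are linked among participants trained alike. The partial correlation has mean 0.00 in every case.

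**The case against.** **Pooling is not stated.** A two-variable r computed separately in each arm also fits the text and has no such artefact. The article condenses a fuller protocol, so silence on pooling is not in itself an error. This stands as a condition on the point. The text does fix a two-variable Pearson r, however, and with the by-group split attached only to descriptive statistics, the plain reading is one r per pair over everyone.

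**The effect is small and conditional.** This also stands. The planning effect is set for peak oxygen consumption only; no effect size is given for the other outcomes. MCT is an active comparator and both arms receive standard rehabilitation, and improvement shared by the arms induces nothing. Even with 0.67 SD on both outcomes, about 89% of unlinked pairs would not be significant at 52 completers. The 1 SD case is the upper part of an illustrative range, not a value from the article.

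**The analysis is exploratory.** It is not among the listed aims and is framed as a search for potential associations. That limits the importance of the point but does not remove the better method.

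Two stronger readings are tempting and are not supported:

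- A reader might infer that the artefact always flatters HIIT. Its sign is that of d1·d2. If both effects are favourable, it is negative where a lower score is better (MSIS-29, FSMC, HADS). If one outcome favours HIIT and the other MCT, it runs against the hoped-for direction.
- A reader might infer that fitness and power output will correlate merely because they share a test: "PPO is assessed as the peak wattage achieved during CPET", the same test that yields oxygen consumption. The article states that shared source openly, sets respiratory, heart-rate and exertion criteria for accepting a peak value, and gives no error correlation from which to size an effect. Adjusting for arm would not address it either.

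**Conclusion.** The point holds in conditional form: the stated method cannot separate a link among participants from a difference between arms. If the arms are pooled and both outcomes of a pair differ by arm, as the Discussion gives reason to expect for peak oxygen consumption and cognition, significance is reached about twice as often as the nominal 5% at the planning-scale effect. The inflation is slight for smaller arm differences, absent if only one outcome differs, and substantial only near 1 SD on both.

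This rests on pooling, on reading the planning effect size as Cohen's f, and on applying that effect to a second outcome for which the article gives none. It is a cheap improvement to a secondary exploratory analysis. It does not call the between-group results into question, and it does not show that any particular pair will correlate spuriously.

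**What to change.** In Statistical analysis, replace the two-variable Pearson correlations with partial correlations between changes adjusted for arm or, equivalently for testing, a regression of one change on the other with arm as a covariate. State that the estimate describes association among participants within arms.

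Arm is already recorded, so no new data are needed. The cost is one sentence and one degree of freedom: N − 3 instead of N − 2, which is 49 instead of 50 at 52 completers. Adjustment for arm is sufficient; this point gives no reason to add baseline values as covariates.

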### Data management and confidentiality

Data generation, transmission, storage, and analysis follow Swiss legal requirements for data protection. Personal data are considered confidential and disclosure to third parties is prohibited. The anonymity of participants is guaranteed by utilizing unique subject identification code numbers that are consecutively generated by a computerized list. Personal data and the allocation list are locked separately from anonymized baseline variables and outcome data. Unblinding of outcome assessors towards allocation is permissible upon completion of T_4_. Data of all outcomes as well as case report forms will be archived (1) in folders that are stored in locked study closets, and (2) electronically on personalized password-secured desktop computers. Backups are automatically performed every hour. Access is provided to authorized study personnel, the Clinical Trial Board of the Kliniken Valens hospital group, and the local Ethics committee at all times for purposes of trial-related monitoring, audits, review, and regulatory inspections.

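### The .05 level covers all analyses and so also the planned interim look; if superiority can be claimed at either look, two-sided type I error is about 8.3%, not 5%

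*Protocol article*

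**What the plan says.** The relevant statements are all in the protocol article.

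- **Statistical analysis, level:** "For all analyses, the level of significance is set at" p = .05. No analysis is exempted.
- **Statistical analysis, looks:** in addition to the final analysis, "one interim analysis will be performed upon collection of 50% of participant data", with sizes given by arm (15 HIIT, 16 MCT). The article gives no purpose, separate level, alpha allocation or stopping rule for this look. Bonferroni correction is named only for pairwise comparisons of estimated marginal means, not for the two looks.
- **Sample size calculation:** "Power was set at 80% and alpha at 0.05". The whole 0.05 goes to one test.
- **Aim, study design, and setting:** the trial is a superiority trial, with HIIT hypothesized to be better than MCT.
- **Data management and confidentiality:** "Unblinding of outcome assessors towards allocation is permissible upon completion of T_4". The article does not say whether this means each participant's T4 or the last participant's T4.

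**The concern.** An interim analysis is one of the analyses to which the .05 rule applies. Read literally, the plan permits a test of the primary comparison at .05 at mid-trial and again at .05 at the end. Two chances to declare superiority at an unadjusted level raise the false-positive rate above the 5% used in planning.

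The Discussion expects the superiority design to yield explicit training recommendations for clinical practice, so the error rate of the primary claim matters. As the text stands, a reader cannot tell whether that claim carries 5% or about 8.3% error.

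The interim sentence alone would not be a finding, since a condensed article may leave interim details to the full protocol or SAP. The difficulty is that the article also fixes a level for all analyses. A SAP that spent alpha across the two looks would have to contradict that sentence.

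**Working it through.** **Inputs**

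- Level at each look: .05 (Statistical analysis).
- Looks: one interim, one final (Statistical analysis).
- Interim size: 15 + 16 = 31. Final size: 30 + 31 = 61 (Sample size calculation).
- Information fraction: t = 31/61 = 0.508; the article's rounded description is 0.50.
- Sidedness: not stated. The planned group-by-time F-test is two-sided by construction, so the two-sided case comes first and the HIIT-favouring direction second.

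**Step 1. The plan's own error rate.** One two-sided test with critical value 1.96 has 5% error, which is the planning alpha. It holds for a single look.

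**Step 2. Two looks at .05.** Under the null hypothesis the two test statistics Z1 and Z2 are approximately bivariate normal with correlation √t = √(31/61) = 0.713. Then

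P(reject at either) = P(|Z1| > 1.96) + P(|Z2| > 1.96) − P(both exceed 1.96 in absolute value).

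The bivariate normal integral gives:

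| Information fraction | Two-sided error | False claim favouring HIIT |
|---|---|---|
| 31/61 | 0.0828 | 0.0414 |
| 0.50 | 0.0831 | 0.0416 |

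At 31/61 the joint term is 0.0172, so 0.05 + 0.05 − 0.0172 = 0.0828. A simulation of 400,000 trials, with t-tests at 15 vs 16 and then at 30 vs 31, gave 0.0824 two-sided and 0.0415 in the HIIT direction. The nominal rates are 0.05 and 0.025.

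**Step 3. No efficacy claim at the interim.** Only the final test can reject, so its error stays at 5%. The inflation depends entirely on whether the interim can support a claim.

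**Step 4. Levels that restore 5% overall at t = 31/61.**

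| Rule | Interim level | Final level |
|---|---|---|
| Haybittle-Peto | .001 | .0498 |
| O'Brien-Fleming type | .0055 | .0479 |
| Pocock type | .0295 | .0295 |

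With .001 at the interim and the final level left at .05, the total is 0.0502. The reduction to .0498 removes that small excess.

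**Step 5. What an efficacy interim could show.** This step reads the stated effect size of 0.15 as Cohen's f, the usual G*Power metric, which the article does not name. The noncentrality is λ = f²·N·2/(1 − ρ), with ρ = 0.6 and 1 and N − 2 degrees of freedom. For N = 31, λ = 0.0225 × 31 × 2/0.4 = 3.49 and power at .05 is 44%. With about 26 analysed (31 × 0.85, the plan's own drop-out), λ = 2.93 and power is 38%. An interim at .05 would more likely miss the planned effect than detect it.

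On the same reading, the stated total of 61 does not reproduce: 80% power needs 72 completers, or 72/0.85 ≈ 85 with drop-out. That is a separate matter, because the 8.3% depends on the information fraction and not on the sample size.

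**The case against.** **The interim may not be an efficacy test.** The article names no interim endpoint, between-arm comparison, early stopping or superiority claim. The counts 15 and 16 fix when the look happens; they do not show that the arms are compared. A reader might infer that the trial's false-positive rate simply is 8.3%. The documents do not support that. The figure is conditional, and a descriptive, blinded or futility-only look leaves the final test at or below 5%. This objection stands and limits the point to a conditional one.

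**The hypothesis is directional.** The two-sided 8.3% also counts false findings that MCT is better. For a false claim favouring HIIT the rate is about 4.1% against 2.5%. This stands too, so both figures are given; the relative inflation is about the same.

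**Interim details belong elsewhere.** The Data Availability section says that a full protocol and a Clinical Trial Board charter exist, and they may define the interim. One can also read the .05 sentence as the general level for the outcome models described just before it. This excuses the missing purpose and boundary. It does not excuse a rule stated for all analyses, with an interim analysis announced in the same paragraph and no exception made.

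**Assessor unblinding.** A reader might infer that assessors are progressively unblinded and that this biases later exercise tests. The documents do not establish this. The T4 wording is ambiguous between participant and trial level. Knowing a finished participant's arm does not directly reveal a later one's, given stratified randomization with random block sizes and a sequence withheld from study staff. No encouragement is described for the exercise test, and it is not permitted in the walk test. What remains is a wording ambiguity.

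**Conclusion.** The point holds in conditional form. As written, the .05 level applies to the interim as well as the final analysis, and the planning alpha makes no allowance for two looks. If superiority may be claimed at either look, which the text permits without stating it, the overall two-sided type I error is 8.3% instead of 5%, or about 4.1% instead of 2.5% for a false claim that HIIT is superior. If the interim carries no efficacy claim, there is no inflation.

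The figures rest on normal approximations at 31 of 61 participants and change little at exactly one half. They do not depend on the effect size or standard deviation. The interim power of 38% to 44% does depend on reading the effect size as Cohen's f.

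The correction is still timely on the article's own account. The Study status section reports 23 participants recruited by March 2023, fewer than the 31 needed for the interim, so at that date the rule could be fixed before anyone saw interim results.

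**What to change.** Amend the interim sentence in the Statistical analysis section to state one of two rules:

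- **(a) No efficacy test.** The interim is pooled and blinded, covering accrual, drop-out, safety and the overall standard deviation, with no between-arm efficacy test. The final analysis stays at .05. This costs no alpha.
- **(b) Efficacy test.** The interim uses the Haybittle-Peto rule: superiority may be claimed only at p < .001, and the final analysis is tested at .0498. The cost is a marginally stricter final level.

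Under (b), the sentence that sets .05 for all analyses should exempt these two tests of the primary comparison.

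As a minor separate clarification, the Data management and confidentiality section should say that assessors may be unblinded only after the last participant's T4. The cost is that assessors stay blinded for longer. Each change takes a sentence or two.
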